### Physiotherapist training

A minimum of twelve physiotherapists per group (aim of *n* = 6/group per site) are employed to provide the intervention. The trial’s EPIPHA-KNEE intervention is provided by physiotherapists with a minimum of 5 years clinical experience who have undertaken high-level pain education training (Explain Pain course; NOIgroup). The trial’s control intervention is also provided by physiotherapists with a minimum of 5 years clinical experience, but who have not undertaken high-level pain education training.

Prior to trial commencement, physiotherapists in the EPIPHA-KNEE group complete intensive training in PSE specific to OA (i.e., the EPIPHA-KNEE intervention), involving pre-reading of key papers (4 h) and attendance at two full days (16 h) of in-person group training. The training days are delivered by leading experts in pain science, health education, and osteoarthritis. The training includes orientation to the content of the educational component of the trial intervention (i.e. educational objectives for participants), and advanced training in skills to promote conceptual change and self-regulated learning.

Physiotherapists in both intervention groups also complete online training modules (5.5 h EPIPHA-KNEE group, 4 h Control group) for: i) trial procedures (including key trial contacts, mandatory reporting to research team, ethical and confidentiality matters); ii) the relevant educational intervention (including specific objectives for each treatment session and instructions on how to individualise education to the participant); iii) the graded walking program (the guiding principles, ideal prescription, how to individualise to the participant, and how to vary if flare-ups occur); iv) the strengthening exercise program (as per walking program); v) intervention delivery (how to integrate the three components of Education, Walking program, and Strengthening program within each session, how to use the Case Notes); vi) telehealth sessions (tips to ensure telehealth runs smoothly). Lastly, formal competency checks of the physiotherapists in both groups are undertaken by the research team via: i) review of physiotherapist’s verbal/written answers to questions about the trial protocols and the interventions; ii) auditing of (and feedback on) audio-recorded intervention sessions for a pilot participant treated by each physiotherapist.

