### Trial sample size

The Osteoarthritis Research Society International (OARSI) recommends an effect size (d = mean difference/SD_difference_) of 0.5 as the minimal clinically important difference (MCID) for outcomes in OA trials [97]. Past work has estimated that PSE increases physical activity by 1165 steps/day (SD = 985) in people with back pain, producing a large effect (d = 1.18) [39]. Given ~ 850 steps/day increase in knee OA populations after intervention (SD_difference_ = 950) [98] and our pilot data, we anticipate a moderate-large effect in the PSE group and a small effect in the control group at 12 months; consistent with a between group effect size of 0.5. Analysing these data using linear mixed effects modelling, to detect an effect size of d = 0.5 for physical activity using alpha = 0.05, power = 0.90, 4 time points, repeated measures correlation = 0.7, and 20% loss to follow-up [98], 156 participants (78/group) are needed. To additionally adjust for clustering based on therapist (~ 12 therapists/group; ~ 6.5 patients each; ICC = 0.05 [99]), 198 participants (99/group) are then required. The MCID for WOMAC Total at 12 months in people with knee OA undergoing an exercise intervention is 11.5 [100, 101], and given a between group SD from our pilot data of 13.8 (d = 0.83) [42], we are also sufficiently powered for this outcome. We did not adjust the alpha level for multiple comparisons (two primary outcome measures) in our power analysis, but we will present unadjusted *p*-values and confidence intervals for meaningful interpretation.

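### The clustering step behind 198 does not reconcile: 12 therapists with 6.5 patients each is 78 per group, but 99 per group is 8.25 each

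*Protocol article*

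**What the plan says.** The Trial sample size section of the protocol article gives the calculation in two stages. The first sets out "to detect an effect size of d = 0.5 for physical activity", "using alpha = 0.05, power = 0.90", and "4 time points, repeated measures correlation = 0.7", under a mixed model, "and 20% loss to follow-up [98], 156 participants (78/group) are needed". The second adjusts for "clustering based on therapist (~ 12 therapists/group; ~ 6.5 patients each; ICC = 0.05 [99]), 198 participants (99/group) are then required".

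The Physiotherapist training section describes the staffing: "A minimum of twelve physiotherapists per group (aim of *n* = 6/group per site) are employed to provide the intervention".

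The article does not say how the 20% loss was applied, or whether the caseload of about 6.5 counts recruited or analysed patients.

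**The concern.** The three printed quantities in the second stage should fit together: therapists per group, patients per therapist and patients per group. They do not. The caseload used for the design effect belongs to the sample before it was enlarged. With a fixed number of therapists, enlarging the sample enlarges each therapist's caseload, which raises the design effect, so the calculation has to be repeated at the new caseload or solved in one step.

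At stake is whether 198 delivers the stated 90% power on the article's own inputs. A reader who checks the arithmetic will find that it does not on the plainest reading, which counts recruited patients over 12 therapists.

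**Working it through.** **Inputs from the Trial sample size section.** 78 per group before clustering; k = 12 therapists per group; m = 6.5 patients each; ICC = 0.05; final size 99 per group; power 0.90; alpha 0.05 (taken as two-sided, which the section does not state).

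**Reproducing the stated figure.** Design effect = 1 + (m − 1) × ICC = 1 + 5.5 × 0.05 = 1.275. Then 78 × 1.275 = 99.45 per group, or 156 × 1.275 = 198.9 in total. The article prints 99 and 198, so the result was rounded down.

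**Checking the caseload.** 12 × 6.5 = 78, the pre-inflation size. The final size gives 99 / 12 = 8.25.

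**Recomputing on recruited patients, accepting 78.**
- At m = 8.25 the design effect is 1 + 7.25 × 0.05 = 1.3625. Then 78 × 1.3625 = 106.3, so 107 per group (214 in total).
- Solved jointly with 12 therapists: n = 78 × [1 + (n/12 − 1) × 0.05], so n = 78 × 0.95 / (1 − 78 × 0.05/12) = 74.1 / 0.675 = 109.8. That is 110 per group (220 in total).

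**Power at 99 per group, taking 78 as giving exactly 90%.** The effective size is 99 / 1.3625 = 72.7. The standardised effect at 90% power is 1.960 + 1.282 = 3.242. Scaled, it is 3.242 × √(72.7/78) = 3.129. Power = Φ(3.129 − 1.960) = Φ(1.169), about 87.9%.

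**The same on analysed patients.** With 20% loss, 99 × 0.8 / 12 = 6.6 per therapist and the design effect is 1.28. Then 99 / 1.28 = 77.3 against 78, and power is about 89.8%. Solved jointly, n = 74.1 / (1 − 78 × 0.05 × 0.8/12) = 74.1 / 0.74 = 100.1, so 101 per group.

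**Therapists needed to hold the caseload.** 99 / 6.5 = 15.2. Fifteen therapists per arm would carry 6.6 recruited patients each.

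**The loss step.** The article does not print its base formula. One that fits the inputs is 2 × 3.242² / 0.5² × (1 + 3 × 0.7)/4 = 84.06 × 0.775 = 65.15 per group before loss. Three ways of applying 20% loss are:
- Multiplying by 1.2: 65 × 1.2 = 78 (65.15 × 1.2 = 78.2).
- Dividing by 0.8: 65.15 / 0.8 = 81.4, so 82.
- Entering retention by visit as 1, 0.8, 0.8, 0.8 for the four-visit mean. The variance factor is [1 + 3 × 1.25 + 6 × 0.7/√0.8 + 6 × 0.7/0.8] / 16 = 0.9185, and 84.06 × 0.9185 = 77.2, so 78.

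The first and third both reach the printed 78.

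**The case against.** The strongest reply is that the figures are approximate and that the relevant caseload is the number analysed. On that count 99 per group gives 6.6 per therapist, close to 6.5, and almost nothing is lost. With the by-visit loss calculation (77.2 needed, 77.3 available) power is just over 90%. This stands as a limit on the size of the problem. It does not explain the printed 6.5, which is exactly 78/12, where 78 already includes the allowance for loss; analysed patients from that base would be 62.4/12 = 5.2 each.

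The training section also gives twelve therapists as a minimum, so more therapists and smaller caseloads are possible. That is fair, but the calculation itself uses about 12, and the staffing aim of six per group per site agrees with it.

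A reader might go further and infer that the loss step is wrong too, because 65 × 1.2 = 78 while division by 0.8 gives 82. The document does not support that conclusion. It does not state the method, the match with 1.2 is only numerical, and a by-visit attrition formula also gives 78. That formula does count baseline as a fully retained outcome visit, which is reason to ask how the loss entered but not to call the step an error. For the same reason the text does not establish that 198 misses 90% power on every reading.

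**Conclusion.** The clustering step is wrong as printed. Therapist count, caseload and final sample size cannot all hold for recruited patients, and the design effect was not updated for the enlarged sample. Accepting 78 per group, 12 therapists and an ICC of 0.05, the requirement is 107 per group by one update or 110 by joint solution, and 99 gives about 88% power. If caseload means analysed patients, power is about 90% and the gap is one or two participants per group. Rounding 99.45 down to 99 is a separate slip of less than one participant per group. The effect on the trial is modest. What needs correcting is a printed sample size and power that do not follow from their printed inputs. The 20% loss step remains an open question, not a finding of error.

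**What to change.** Keep 198 and restate the calculation:
- Give the caseload that 99 per group implies, and say whether it counts recruited or analysed patients.
- Compute the design effect at that caseload, round up, and report the power that 198 delivers (about 88% on the recruited basis with 12 therapists).
- Alternatively, state the number of therapists per arm, about 15, that holds the caseload near 6.5.
- Add one sentence saying how the 20% loss entered the 78 per group.

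The cost is a few sentences of restated figures. If the restatement is chosen, neither recruitment nor staffing changes. If the therapist number is chosen, it should match the number actually engaged.

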### Analysis

A full statistical analysis plan will be published prior to undertaking the formal analysis of collected data (including description of secondary analyses). The proposed preliminary analysis plan is detailed below.

#### Primary analysis

Data will be analysed using intention-to-treat principles with the trial biostatistician blinded to group allocation. We will use linear mixed effects models with random intercepts for individuals (to account for correlation for repeated measures) and will analyse the effect of treatment separately for each outcome. The model will include terms for stratification factors of sex and site. A time-varying, group specific effect (for each group) will be included as covariates for participants with restricted physical activity as a result of location-specific COVID-19 restrictions (based upon official activity restrictions and/or participant reported restrictions; assessment detailed above). Statistical significance will determine whether group-specific covariates or even any COVID-19 related effects are warranted for model parsimony. Multiple imputation will be used for missing data if the assumptions are reasonable [102]. We will construct linear contrasts to compare the adjusted mean change in outcome from baseline to each time point between the EPIPHA-KNEE group and the control group (and 95% confidence interval) to obtain estimates of the intervention effect. We will analyse primary and secondary outcomes without adjustment for multiple measures, but we will present unadjusted *p*-values and confidence intervals for all pre-specified analyses [103, 104] so readers can make adjustments (e.g., Bonferroni) at the level of Type I error control that they wish, at risk of making Type II errors.

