### Randomisation allocation concealment and blinding

Following completion of the baseline assessments (questionnaires, objective assessment, accelerometry), participants are randomised to either the EPIPHA-KNEE group or the Best Practice Education/Activity Control group. The computer-generated randomisation schedule was prepared by the study biostatistician using Research Randomizer [50], with randomly selected permuted blocks of varying size (4 and 6) and using a 1:1 ratio to the two treatment groups within four strata (sex and site: Adelaide, Melbourne). The EPIPHA-KNEE intervention and the Best Practice Control intervention are provided by different physiotherapists located at different clinic sites. Thus, once allocated to an intervention group, participants choose one of the candidate physiotherapy clinics that provide that intervention to attend (i.e., the clinic that is most convenient for them).

Allocation is concealed using central automated allocation, with security in place to ensure data cannot be accessed or influenced. The randomisation schedule is stored within a password-protected electronic system (REDCap). A hard copy of the raw randomisation schedule is also stored in a secure location at each site should the electronic system fail. Only the unblinded Research Leads ([name] in Adelaide, KB in Melbourne) have access to raw copies of the randomisation schedules. The trial coordinators at each site (Adelaide, Melbourne), randomise participants to intervention group. Notably, while the trial coordinators determine if a participant is eligible for inclusion in the trial, due to inaccessible online randomisation with use of randomly permuted block size and stratification, they are unaware when this decision is made to which group the participant will be allocated. Once randomised, the (now) unblinded trial coordinators at each site (Adelaide, Melbourne) coordinate treatment appointment scheduling with the appropriate physiotherapist as identified by the participant.

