### Treatment fidelity

Following trial commencement, the trial physiotherapists can discuss any issues that arise with delivering the intervention with the research team. Trial physiotherapists can contact the research team through the trial by email or telephone. Additionally, regular meetings via Zoom are held with the trial research team and each intervention group of physiotherapists (separately). These regular meetings also allow the opportunity for therapists to provide feedback or discuss any issues arising. A random sample of treatment sessions (minimum of one for each therapist) will be audio recorded to allow an audit of intervention fidelity for each group. Each physiotherapist and physiotherapy clinic will provide only one of the two study interventions. Therapists’ case notes for each session, recorded via standardised templates, will also be used to evaluate intervention fidelity (e.g., the exercises and walking prescribed).

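### The sample size is inflated for clustering by therapist, but the preliminary primary model names no therapist term; carried into the SAP as written, it would give a two-sided type I error of about 8–9% at the protocol's own ICC

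*Protocol article*

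**What the plan says.** **Design.** Under Treatment fidelity: "Each physiotherapist and physiotherapy clinic will provide only one of the two study interventions". Under Randomisation allocation concealment and blinding, once allocated, "participants choose one of the candidate physiotherapy clinics that provide that intervention to attend". Therapists and clinics are therefore nested in arm with no crossing, and are chosen after baseline and after randomisation. Physiotherapist training plans at least twelve therapists per group.

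**Sample size.** Trial sample size first reaches 156 participants (78 per group) and then makes a separate allowance: "To additionally adjust for clustering based on therapist (~ 12 therapists/group; ~ 6.5 patients each; ICC = 0.05"), which gives 198 (99 per group).

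**Model.** Under Primary analysis: "We will use linear mixed effects models with random intercepts for individuals (to account for correlation for repeated measures"). The other terms named are the stratification factors (sex and site) and COVID-19 covariates. Treatment effects are contrasts of adjusted mean change from baseline to each time point. No therapist or clinic term, cluster-robust standard error or other clustering adjustment appears anywhere in the Analysis section. Site is the Adelaide/Melbourne stratum, so it cannot absorb variation among some 24 therapists.

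**Status.** The Analysis section calls this plan preliminary and says a full SAP will be published before the formal analysis.

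**The concern.** When each therapist delivers only one arm, differences between therapists enter the between-arm contrast directly. They do not average out within arms as they would if therapists delivered both interventions. The individual random intercept is there to handle repeated measures on the same person. It does not represent the correlation among different people treated by the same therapist.

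A larger sample preserves power when the analysis models the clustering. It does not protect type I error when the analysis ignores it. Under the model as written, the 42 participants added for clustering (198 − 156) would be analysed as independent. The p-values and confidence intervals for both primary outcomes would then overstate precision. Both outcomes are to be tested without multiplicity adjustment, so nothing else in the plan offsets this.

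**Working it through.** **1. Reproduce the plan's figures.** Inputs from Trial sample size: a standardised effect of 0.5, a significance level of 0.05, 90% power, four visits correlated at 0.7, and 20% attrition. A two-sided test is assumed, since sidedness is not stated.

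- Two-sample n per arm: 2 × [(1.960 + 1.282) / 0.5]² = 84.06.
- Four visits at correlation 0.7: × (1 + 3 × 0.7) / 4 = × 0.775, giving 65.1.
- Loss to follow-up, applied as × 1.2: 78.2 per arm, about 156 in total. This matches.
- Design effect: 1 + (6.5 − 1) × 0.05 = 1.275. Then 156 × 1.275 = 198.9, against 198 stated. This matches apart from rounding.

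The step from 156 to 198 is therefore the therapist design effect.

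**2. Error rate if the analysis ignores therapist.** Let m be the participants per therapist and DE = 1 + (m − 1) × ICC. The naive standard error is 1/√DE of its correct size, and the true two-sided error is 2 × [1 − Φ(1.96/√DE)].

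At the protocol's ICC of 0.05:

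| m | Source | DE | SE too small by | Type I error |
|---|---|---|---|---|
| 6.5 | stated | 1.275 | 11.4% | 8.3% |
| 6.6 | 99 × 0.8 / 12 | 1.280 | 11.6% | 8.3% |
| 8.25 | 99 / 12, no loss | 1.3625 | 14.3% | 9.3% |

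Over other ICCs, for m from 6.5 to 8.25:

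| ICC | Type I error |
|---|---|
| 0.01 | 5.6–5.8% |
| 0.02 | 6.3–6.7% |
| 0.10 | 11.5–13.6% |

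**3. Simulation check.** Null data were generated with 4 visits, correlation 0.7, 12 therapists per arm and a therapist effect on post-baseline visits (6,000 runs per setting). They were analysed with a random intercept for individuals only, contrasting change to 12 months. With an ICC of 0.05 defined on the change score, rejection was 8.4% at about 6.6 per therapist and 9.8% at 8.25. If 0.05 is instead a share of the raw outcome variance, rejection was 11–12%. A comparison of therapist means rejected in 4.3–5.6% of runs across all settings, so the excess comes from ignoring the clustering.

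**4. Cost of the correct analysis.** With 24 therapists in two arms, the therapist-level degrees of freedom are about 22, with a t quantile of 2.074. Relative interval width is √1.28 × 2.074 / 1.960 = 1.131 × 1.058 = 1.197. That is about 20% wider: about 13% from the design effect, and the rest from the degrees of freedom.

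**The case against.** The strongest objection is that this is an omission from a plan labelled preliminary. The article does not say the individual intercept is the only random effect, the sample size section shows that the authors had therapist clustering in mind, and random-effects detail is commonly left to a SAP, which is not at hand. This stands to the extent that the documents do not show the final analysis will be wrong, and the point has to be conditional. It does not remove the conflict. The article is not silent on random effects: it names one, gives its purpose and lists the other terms, and that model does not match the design that the sample size was built on.

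Second, the error rate depends on an ICC that is only a planning value. That stands, and so the range is given. The Discussion notes at least 3 months between the last in-person session and the primary time point, so a smaller therapist effect at 12 months is plausible, though not established. Twelve therapists per group is also a minimum: at ICC 0.05 and 79.2 analysed per arm, 15 per arm gives 7.5% and 18 gives 7.0%.

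Third, a reader might infer that the model is tilted towards finding a benefit of EPIPHA-KNEE. The documents do not support that. An understated standard error inflates rejection in both directions equally and does not bias the estimate.

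A reader might also assume that every randomised participant has a known therapist. The article does not say so. The clinic is chosen after randomisation, so someone who withdraws before choosing would have none and would still belong in the intention-to-treat analysis.

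**Conclusion.** The point holds. Trial sample size and Primary analysis conflict on therapist clustering, and the model followed as written would not keep its nominal error rate. At the protocol's ICC of 0.05, with 12 therapists per arm, the standard error is about 11–14% too small and the two-sided type I error is about 8–9% by formula. The error is about 6% if the true ICC is 0.01–0.02 and about 12–14% if it is 0.10. These figures assume a two-sided 5% test, roughly equal caseloads and a therapist effect that acts after baseline. The size depends on the ICC; the direction of the standard-error understatement does not, for any positive ICC. What cannot be concluded is that the trial's final analysis contains the error, because the SAP is not shown.

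**What to change.** Settle the therapist structure in the SAP before analysis, for both primary outcomes and for the secondary outcomes that use the same model:

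- Add a therapist random effect, nested in arm and acting on the post-baseline visits. A therapist intercept that is constant over all visits, baseline included, largely cancels from a change-from-baseline contrast and would leave the problem in place. Alternatively, use baseline as a covariate and fit a therapist random intercept to the follow-up outcomes.
- Specify Satterthwaite or Kenward-Roger degrees of freedom.
- State how participants who withdraw before choosing a clinic are handled.
- State what is done if the therapist variance is estimated as zero. A one-way ANOVA approximation with 24 therapists of about 6.6 participants puts the chance of this at about 21% at ICC 0.05 and 38% at ICC 0.02.

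**Cost.** The change is SAP wording and one variance component. Confidence intervals become about 20% wider than under the individual-only model at ICC 0.05. The increase to 198 covers the design effect but not the small-degrees-of-freedom penalty, so power will be somewhat below what that calculation implies. The simulations showed that a therapist-level analysis holds about 5%; the recommended mixed model was not itself simulated, and a short check in the SAP would be worthwhile.

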Current strategies that aim to increase physical activity in people with OA include structured physical activity interventions targeting aerobic capacity, endurance, and strength [26]. These interventions aim to increase exercise tolerance, strength or overall fitness, maintain or reduce weight, and decrease pain. They have short-term but not long-term effects on physical activity levels [26]. Behavioural interventions, targeting features such as self-efficacy or coping skills to promote self-management, have also been used to increase physical activity. Again, physical activity levels increase in the short term, but decline over time, with no effect after 12 months [27]. Critically, the reduction in benefits from physical activity in OA is directly related to declining rates of adherence [28]. Thus, improving long-term adherence is key to achieving meaningful health and OA-specific benefits. Promoting maintenance of physical activity gains remains a significant challenge – we are still chasing the holy grail of instilling physical activity as a regular part of daily life in people with OA.

A notable similarity amongst most current approaches that aim to increase physical activity is encouraging ‘movement despite pain’ (e.g., behavioural interventions using coping skills), with the ‘promise’ of pain-relieving effects over time. Arguably, such approaches may seem counterintuitive to people with knee OA as long as they consider pain to be a marker of joint damage [29]. For instance, if people believe that increases in pain represent more joint damage and that physical activity may be unsafe for their joint, then it is unlikely that they will engage in or adhere to activity programs that suggest that they should move despite having pain [12]. Further, if these unhelpful beliefs are not challenged, then flare-ups of pain that often occur with activity programs may derail long-term adherence [30]. Although including general education within physical activity programs is recommended by OA practice guidelines [31], we contend that current education may be suboptimal. Current education largely focuses on how to accurately and safely perform activity and the health and OA-specific benefits of activity [32]. Such education does not improve poor long-term activity adherence [33].

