### Outcomes

Table 5 provides the full list of outcome measures and time points of assessment. Our primary and secondary outcome measures are measured at baseline, 12 weeks, 6 and 12 months.

**Table 5 Tab5:** Summary of measures to be taken

Domain	Data collection instrument	Time points				
		Baseline	After 1st treatment session	12 weeks	6 M	12 M

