### Primary outcomes

The primary outcomes are: i) average daily step count assessed over 7 consecutive days via wrist-worn accelerometry (Actigraph GT9X Link, Pensacola, FL); and ii) overall knee symptoms measured via the Western Ontario and McMaster Universities (WOMAC) Osteoarthritis Index [62]. The primary timepoint for both outcomes is 12 months.

For daily step count, participants wear the accelerometer on their non-dominant wrist at all times (removal only for shower or during water-based activities). Data are collected from the device in 60 s epochs. A paper-based activity log is provided to participants to capture times they go to bed at night and get up from bed in the morning, as well as times the accelerometer was removed and then placed back on (particularly if taken off when sleeping). Valid wear time is operationalised as having ≥10 h of waking wear time for a minimum of 4 days (3 weekdays and 1 weekend day) [63, 64]. Average daily step count is calculated as the weighted average (5:2) of weekday and weekend step counts. We chose daily step count as a primary outcome based on its: i) health benefits in knee OA (increased physical activity via walking improves both pain and function [65], and even a moderate increase in physical activity [1000 steps/day] reduces risk of functional decline [66]); and ii) established reliability/validity in knee OA [67].

The WOMAC is a disease-specific self-report questionnaire that includes pain (5 items), stiffness (2 items), and physical function (17 items) subscales. Items are scored from 0 to 4, giving a range of possible scores from 0 (no symptoms or dysfunction) to 96 (maximal symptoms and dysfunction). It has demonstrated validity, reliability, and responsiveness [68]. The use of the total score for primary outcomes is supported by the scale creators.

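### The random intercept, the only within-person structure the article names, gives too small a standard error for the 12-month contrast if correlation between visits fades over the year

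*Protocol article*

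**What the plan says.** All references are to the protocol article.

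- **Model (Primary analysis).** The plan is to use linear mixed models with "random intercepts for individuals (to account for correlation for repeated measures"), fitted separately to each outcome with terms for sex and site and COVID-19 covariates. No random slope, serial residual correlation, unstructured matrix or robust standard error is mentioned.
- **Effect estimate (Primary analysis).** The effect comes from "linear contrasts to compare the adjusted mean change in outcome from baseline to each time point between the EPIPHA-KNEE group and the control group".
- **Schedule (Outcomes).** "Our primary and secondary outcome measures are measured at baseline, 12 weeks, 6 and 12 months".
- **Primary time point (Primary outcomes).** "The primary timepoint for both outcomes is 12 months".
- **Planning assumptions (Trial sample size).** The calculation takes "d = 0.5 for physical activity using alpha = 0.05, power = 0.90, 4 time points", followed by "repeated measures correlation = 0.7, and 20% loss to follow-up". One correlation is used for the whole schedule.
- **Status (Analysis).** The plan is described as preliminary, with a full SAP to be published before formal analysis.

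**The concern.** A random intercept with independent residuals of constant variance has two covariance parameters. It implies that two measurements 12 weeks apart are exactly as correlated as two measurements 12 months apart. The fitted within-person variance is then an average over all six pairs of visits, and the model uses that average to compute the standard error of every change contrast.

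The contrast that matters here is not an average one. Baseline to 12 months is the longest interval in the schedule. If within-person correlation falls as the interval lengthens, this pair lies below the average, and the model credits it with more correlation than it has. Under that condition, and with equal variances, the error runs in one direction: the standard error is too small, the confidence interval too narrow and the p-value too low.

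The same model serves both primary outcomes. The article also plans to report unadjusted p-values and confidence intervals so that readers can apply their own multiplicity correction. That works only if the unadjusted p-values are sound.

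**Working it through.** **1. The plan's own figures.** The article does not print its formula, but an equal-correlation calculation reproduces its numbers.

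- Two-sample size per group: 2 × ((1.960 + 1.282) / 0.5)² = 84.06.
- Factor for 4 visits with one common correlation of 0.7: (1 + 3 × 0.7) / 4 = 0.775, so 84.06 × 0.775 = 65.15.
- Dropout applied as × 1.20: 78.2 per group. The article states 78 per group, 156 in total.
- Therapist design effect: 1 + (6.5 − 1) × 0.05 = 1.275, so 78 × 1.275 = 99.45. The article states 99 per group, 198 in total.

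The planning therefore fits the same equal-correlation assumption that the random intercept imposes. It offers no information on whether correlation fades.

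**2. Variance of the 12-month contrast.** Take complete data, a separate mean for each group and visit, common variance σ², and n per group. Let r̄ be the average of the six pairwise correlations and r₀₁₂ the baseline-to-12-month correlation.

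- Variance reported by the random-intercept model: 4σ²(1 − r̄) / n.
- True variance: 4σ²(1 − r₀₁₂) / n.
- Ratio of model variance to true variance: (1 − r̄) / (1 − r₀₁₂).
- True two-sided type I error: 2 × [1 − Φ(1.96 × √ratio)].

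**3. Numbers.** r̄ = 0.7 is the article's figure. The values of r₀₁₂ are assumptions.

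| r₀₁₂ | Variance ratio | SE ratio | Type I error |
|---|---|---|---|
| 0.70 | 0.30/0.30 = 1.00 | 1.00 | 5.0% |
| 0.65 | 0.30/0.35 = 0.86 | 0.93 | 7.0% |
| 0.60 | 0.30/0.40 = 0.75 | 0.87 | 9.0% |
| 0.55 | 0.30/0.45 = 0.67 | 0.82 | 11.0% |

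The correct standard error is 1/0.926 = 1.08 to 1/0.816 = 1.22 times the model's over the range 0.65 to 0.55.

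**4. Check by simulation.** A random-intercept model was fitted by REML to data with no treatment effect, 99 per group, 20% monotone dropout and 1,500 runs per pattern. The Monte Carlo standard error is about 0.6 percentage points at a 5% rate: √(0.05 × 0.95 / 1,500).

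| Assumed pattern | r̄ | r₀₁₂ | Mean model SE | Actual SE | Type I error |
|---|---|---|---|---|---|
| All pairs 0.7 | 0.70 | 0.70 | 0.119 | 0.117 | 4.8% |
| Stable part plus decaying part | 0.65 | 0.55 | 0.127 | 0.146 | 8.7% |
| Continuous-time AR(1) | 0.70 | 0.50 | 0.118 | 0.152 | 12.8% |

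The formula in step 2 gives 8.4% and 12.7% for the last two patterns, so dropout at the planned rate hardly alters the result. The AR(1) pattern is a steep case and is shown only as an outer bound.

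**The case against.** The strongest reply is that the article does not say the random intercept is the whole covariance model. A random intercept can be combined with serial or heterogeneous residuals, or reported with robust standard errors. The plan is labelled preliminary, and residual structure and type of standard error are commonly left to the SAP, which is not shown. This limits the point but does not remove it. The article does not leave the handling of repeated measures open: it names the random intercept as the device for it. The point is about that stated choice, and it lapses if the SAP adds a structure that lets the 12-month correlation differ, or uses robust standard errors.

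The second reply is that fading is undocumented, and this stands in full. A reader might infer that type I error exceeds 5% for both primary outcomes. The documents do not support that, because their only correlation is a single 0.7. Fading is not certain either. For step count, baseline and 12 months fall in the same season and 6 months in the opposite one. With r̄ = 0.70 and an assumed r₀₁₂ of 0.72, the ratio is 0.30/0.28 and type I error is 4.2%, slightly conservative.

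A reader might also take the Background's account of earlier behavioural interventions, "physical activity levels increase in the short term, but decline over time, with no effect after 12 months", as evidence of fading. It describes mean activity. A falling mean is absorbed by the time effects and says nothing about correlation within a person. Nor do the documents show that variances grow over follow-up.

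**Conclusion.** The point holds in conditional form. Read plainly, the stated model ties the standard error of the 12-month contrast to the average correlation over all visit pairs. If the baseline-to-12-month correlation is below that average, the standard error at the primary time point is too small. At an average of 0.7, the true type I error is about 7% to 11% for a correlation of 0.65 down to 0.55, and exactly nominal if there is no fading. These figures assume equal variances across visits, independent residuals and model-based standard errors. The decay values are assumptions, not figures from the trial. This is a worthwhile improvement at low cost, not a demonstrated error in the trial's inference.

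**What to change.** In the SAP, replace the participant random intercept with an unstructured within-person covariance matrix across the four visits, with Kenward-Roger degrees of freedom. Keep any therapist-level random effect alongside it. This lets the baseline-to-12-month correlation and the variance at each visit be estimated instead of imposed.

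Name the fallback for non-convergence in advance: the random intercept with robust standard errors clustered at the highest level of clustering in the design.

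The change costs a sentence or two of SAP wording before analysis. Four visits need 4 × 5 / 2 = 10 covariance parameters against 2 for the random intercept, so eight more, which is modest with 198 participants. If correlations and variances are in fact equal, the price is a small loss of efficiency.
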